### Waiting list condition

The control condition includes a WLC. At 5 months after start (i.e., T4) participants in the WLC receive the opportunity to follow the intervention without email guidance by a therapist. They neither receive a welcome letter at the start, which means that they only read the introduction about the training before starting.

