Even though online interventions are relatively new, several such interventions have demonstrable effectivity in improving QoL in cancer patients and survivors [28, 30–32]. A randomized controlled trial (RCT) has shown that the use of an online CBT intervention significantly improved CIPN pain intensity and may be effective [27]. Furthermore, research has shown that online interventions based on ACT are capable of improving pain intensity, pain interference, pain catastrophizing, disability, depression, anxiety, psychological inflexibility, and QoL in chronic pain patients with a variety of pain diagnoses (e.g., fibromyalgia, rheumatoid arthritis, and back complaints) [33, 34]. These findings suggest that an online self-help intervention based on ACT might be effective for adult cancer survivors with chronic painful CIPN as well. However, effects may differ between patients, since previous research has shown factors such as pain intensity, depressive and anxiety symptoms, and emotional well-being to predict the effectiveness of online ACT for chronic pain [35], and the extent to which patients benefit from the online intervention may hence vary. Furthermore, there may also be differences in the effectiveness with different types of the online intervention, namely with or without guidance. Earlier research has shown that guidance, including feedback, explanations, motivations and reminders, improves treatment effects compared to unguided interventions [36, 37]. The primary aim of this study researching the online intervention named ‘Embrace Pain’ is to reduce pain interference in cancer survivors with chronic painful CIPN. To study this, three objectives have been formulated:*Objective 1:* To examine the effectiveness of an online self-help intervention based on ACT for reducing pain interference in cancer survivors with chronic painful CIPN in a randomized controlled trial (RCT) and compare this to a waiting list condition (WLC).*Objective 2:* To examine which baseline demographic, clinical, and psychosocial factors may moderate the effectiveness of an online self-help intervention based on ACT.*Objective 3:* To examine the extent to which effects differ between guided and unguided versions of the online self-help intervention based on ACT.

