### Randomization

When the patient is admitted to the study, the patient will receive confirmation of participation, the result of randomization, and the baseline questionnaire (T0b). Patients will be randomized to receive either ACT or WLC. The study will stratify by age and sex by means of block-wise randomization. An online generator will be used for this. Randomization will be performed by a research associate.

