### Intervention

The experimental condition includes an online psychological intervention with therapist email guidance based on ACT. The intervention can be worked through by the patient from home or at another location of choice, in a webpage or app by logging in with an email and self-created password. Participants receive a welcome letter from the supervisor. It consists of 6 modules which can be worked through in 8 weeks. The intervention primarily consists of text and experiential exercises, complemented with illustrations, metaphors, and audio (mp3) files. Before starting the module, participants read an introduction about the training. The first module includes psychoeducation on neuropathic pain and CIPN (Table 1). Participants will be provided with information to familiarize themselves with intervention goals and mindfulness exercises central to ACT. In subsequent modules, participants will learn about the aversive effects of pain avoidance, gain insight into their personal values, and work on pain acceptance. Throughout the intervention, participants will exercise to recognize unhelpful thoughts about their pain and learn the difference between the subjective (judging) and objective self, create activities that align with values, and think about concrete actions to prevent relapse. When access to the online environment is terminated, participants can no longer view the online environment or communicate with the supervisor. However, participants can always continue to view the session they submitted.

**Table 1 Tab1:** Schematic overview of modules of the ACT intervention

Module	Therapeutic processes	Information	Assignments	Audio files (mindfulness)
Welcome		Online environment, contact, additional help, other long-term consequences, and tips.		
1: Chronic neuropathic pain	Psychoeducation	CIPN and chronic pain		A: Concentration on breathing
2: On the way to values	Values	Values and valued-based activities	I: Explore your values II: My values III (optional): My values in pictures	A: Body exploration
3: Away from my values	Pain avoidance	Avoidance and managing pain	I: My ways of avoiding II: Moment when I am in pain	A: Concentration on breathing B: Body exploration C: Three-minute breathing space
4: On the road with skills	Commitment and Defusion	Learning how to deal with pain differently	I: Acceptance in action II: Your recurring thoughts of pain III: Is the thought useful? IX (optional): Struggle or open up	A: Allowing what is

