#### Secondary analyses

To assess predictors of effects, steps of a study on predictors of change during CBT for chronic pain will be followed [59]. Pain interference at 3-month follow-up will be used as indicator of treatment effect. Using the PROCESS macro for SPSS [60], linear regression models will be applied (two-tailed). Predictor variables may include sex, age, educational level, number of comorbidities, time since CIPN onset, CIPN symptom severity (EORTC QLQ – CIPN20), quality of life (EORTC QLQ-C30), pain intensity (NRS), psychological distress (HADS), psychological inflexibility (PIPS), mindfulness (FMI-NL), valued based living (ELS), and pain catastrophizing (PCS). They will be selected based on theoretical and empirical considerations.

To assess differences in effects between the guided and unguided version of the intervention, independent samples t-tests and a two-stage hierarchical multiple regression analysis for each primary and secondary outcome will be conducted. Baseline to 3-month follow-up change will be used as the dependent variable. The independent variable will be an intervention dummy variable. Baseline score on the respective outcome measure will be used as control variable. Effect sizes for both conditions will be computed to indicate differences in the magnitude of the effects of online ACT with and without email counseling.

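### Objective 3 ties the unguided course to a five-month wait, attrition and optional uptake, so a guided–unguided difference cannot be credited to email guidance alone

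*Protocol article*

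**What the plan says.** The third objective in the Background of the protocol article is: "To examine the extent to which effects differ between guided and unguided versions of the online self-help intervention based on ACT". The Secondary analyses section plans independent-samples t-tests and a two-stage regression with an intervention dummy, adjusted for the baseline score of the outcome concerned. It states the purpose as follows: "Effect sizes for both conditions will be computed to indicate differences in the magnitude of the effects of online ACT with and without email counseling".

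The Randomization section names two arms only: "Patients will be randomized to receive either ACT or WLC". The guided course is the allocated treatment of the ACT arm. According to the Waiting list condition section, at five months after start, which is T4, "participants in the WLC receive the opportunity to follow the intervention without email guidance by a therapist". The same section then adds a second difference: "They neither receive a welcome letter at the start, which means that they only read the introduction about the training before starting". For the guided course, the Intervention section says: "Participants receive a welcome letter from the supervisor".

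**The concern.** Reading a contrast as the effect of a course with and without email support requires the two groups to be alike in everything but that support. Here they also differ in when the course is offered, in who is still present to be offered it, and in whether taking it up is a matter of choice. If the results follow the wording of the Secondary analyses section, any of these could be reported as an effect of guidance or could hide one.

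The conclusion matters in practice. Objective 3 is the part of the trial that bears on whether therapist guidance is needed when the course is offered more widely. The randomised comparison of ACT with the waiting list under Objective 1 is not affected.

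**Working it through.** The plan gives no figure for this contrast, so there is none to reproduce. The check sets the sections side by side and then asks whether the size of the bias can be found.

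**Step 1. How the two versions are delivered**

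| Feature | Guided course | Unguided course |
|---|---|---|
| How a participant comes to it | Randomised to ACT | Randomised to the waiting list, then offered the course |
| When it is offered | At the start | T4: 2 months to the end of intervention + 3 months = month 5 |
| Who can take it | The whole ACT arm | Waiting-list participants still in the study at T4 |
| Nature of the offer | Allocated treatment | An opportunity, which may be declined |
| Email guidance | Yes, without obligation | No |
| Supervisor's welcome letter | Yes | No |

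Email guidance is one row of several.

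**Step 2. Attrition.** The sample size section allows 30% drop-out: 73 × 0.70 = 51.1, so 51 of 73 per group remain at follow-up and up to 73 − 51 = 22 may be lost. The article does not say how much of this falls before T4. Anyone in the waiting list lost before T4 never becomes an unguided user. Anyone in the ACT arm lost over the same period had already been given the guided course.

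**Step 3. What the planned adjustment removes.** The regression contains the version dummy and the baseline score. This corrects for a difference in that one score between the groups compared. It does not correct for the effect of waiting five months, for reasons for staying in the study, or for motivation to take up a late offer.

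**Step 4. Can the size be found?** Suppose that guidance has no effect, that the course effect is d = 0.50 in anyone who starts, and that everyone offered is analysed. The 0.50 is borrowed from the sample size section. The starting proportions below are assumptions, because the article gives none for either arm. Then

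apparent guidance effect = 0.50 × (proportion starting in ACT − proportion starting in the waiting list).

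- ACT 100%, waiting list 60% to 90%: 0.50 − 0.30 = 0.20 down to 0.50 − 0.45 = 0.05.
- ACT 80%, waiting list 60% to 90%: 0.40 − 0.30 = 0.10 down to 0.40 − 0.45 = −0.05.

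A plausible change in one unknown input reverses the sign. Analysing starters only removes this dilution, but it then compares self-selected users with a randomised arm. If those who wait and still start are unusually motivated, a real benefit of guidance could be hidden.

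**Step 5. Dependence on the outcome window.** The dependent variable is the change from baseline to 3-month follow-up. If that follow-up is T4 (month 5), the waiting list has only just been offered the course, so neither uptake nor the letter can have affected its scores. The test is then guided ACT against waiting. If it means three months after the unguided course, note that the course takes 8 weeks ("It consists of 6 modules which can be worked through in 8 weeks"). Follow-up then falls at about 5 + 2 + 3 = month 10, after the last measurement, T5, at 2 + 6 = month 8. Steps 1 to 4 apply once a window is chosen in which the waiting list has had the course.

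**The case against.** The case on the other side has real force, and most of it limits how far the point can be taken.

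- **The welcome letter.** A reader might infer that withholding it is a needless confounder. The article does not support that. The letter comes from the supervisor, the unguided version has no supervisor, and the letter's content is not described. Both groups read the introduction, and Table 1 lists a welcome section within the course. The letter may fairly be counted as part of guidance.
- **Randomisation.** A reader might infer that allocation to version is wholly unrandomised. That goes too far: the version offered follows from the randomised arm. What is not randomised is a concurrent start and actual uptake.
- **A spurious benefit of 0.05 to 0.20 SD.** This follows only if the whole ACT arm starts while part of the waiting list does not. The article calls drop-out and non-adherence relatively common in online interventions, so full uptake in one arm only is not a neutral assumption.
- **Continuation of the course.** Guidance is partly meant to keep participants motivated, so a difference in persisting with the course may be part of its effect and not bias.
- **Wording.** The objective asks how far effects differ between versions and does not say that a difference is due to guidance alone. However, the Secondary analyses section names the contrast as "differences in the magnitude of the effects of online ACT with and without email counseling", and the article mentions neither the delay nor self-selection as a limit on it.

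The wait, attrition before T4 and optional uptake remain tied to version, and the planned adjustment leaves them in place.

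**Conclusion.** The point holds as a limit on interpretation. The comparison is of immediate guided ACT with delayed, optional unguided ACT among those who remain, and a difference cannot be attributed to email guidance alone. This rests on the design as described and needs no numerical assumption. The direction of bias is open and its size cannot be derived from the document; the figures in the working show only that the sign can change. The missing letter is a minor further difference. The point is secondary to the outcome-window problem, which decides whether the comparison can be made at all.

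**What to change.** In the Background (Objective 3) and in Secondary analyses, describe the comparison as exploratory, between immediate guided ACT and delayed, optional unguided ACT, and state that a difference will not be attributed to email guidance alone. Use matching wording in the abstract. Report the proportion starting the course in both arms. The Process outcomes section already plans to collect the time at which each session was first viewed, so no new data are needed. Resolve the outcome window first, since the new wording has no content while the waiting list is compared at T4.

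The cost is a few sentences and a more modest claim for Objective 3.

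Two further changes are debatable and not required here. Sending the waiting list an adapted letter could split the unguided users: recruitment began in December 2021 and this version is dated 24 May 2022, so the first waiting-list participants may already have reached month 5. Making everyone offered the course the main unguided group would build in the dilution shown in the working, while a starters-only group brings in self-selection. Neither choice turns the contrast into a test of guidance alone.

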### Outcomes

Questionnaires will be completed online via the PROFILES Registry [38]. Patients will receive reminders via email to promote participant retention and complete follow-up. A complete overview of enrolment, interventions, and outcome measurements is shown in Table 2.

**Table 2 Tab2:**
[figure not shown]
Schedule of enrolment, interventions, and assessments

#### Primary outcome

*Pain interference* will be measured using the Multidimensional Pain Inventory, Dutch language version (MPI-DLV) – subscale Interference [39, 40]. The MPI consists of statements rated on a 7-point Likert scale ranging from 0 (no change) to 6 (a lot of change). The subscale Interference focuses on psychosocial aspects of chronic pain, such as functioning in work, homework, and recreational and social activities. The scale consists of 11 items and has been translated/validated into Dutch [39].

#### Secondary outcomes

*Quality of life* will be measured with the European Organization for Research and Treatment of Cancer Quality of Life Questionnaires Core-30 item (EORTC QLQ-C30) [41]. This is a validated 30-item self-report screening scale for QoL in cancer patients including a 4-point Likert scale ranging from 1 (not at all) to 4 (very much) including five subscales (i.e., physical functioning, role functioning, emotional functioning, cognitive functioning, and social functioning) [41].

*CIPN symptom severity* will be measured using the European Organization for Research and Treatment of Cancer Quality of Life Questionnaire-CIPN20 (EORTC QLQ–CIPN20) [42]. This questionnaire is intended to be used as a supplement to the EORTC QLQ-C30. It assesses CIPN-related symptoms as well as functional limitations related to CIPN. The questionnaire has been validated and includes 20 items on a 4-point Likert scale ranging from 1 (not at all) to 4 (very much) including three subscales (i.e., sensory, motor, and autonomic symptoms) [43].

*Pain intensity* will be measured with the Numeric Rating Scale (NRS-11) [44]. This is based on International Association for the Study of Pain (IASP) recommendations for measures in clinical trials on chronic pain [44]. This questionnaire has been validated and includes 2 items on a 11-point Likert scale ranging from 0 (no pain) to 10 (the worst pain possible) [45].

*Psychological distress* will be measured using the Hospital Anxiety and Depression Scale (HADS) [46, 47]. This is based on IASP recommendations for measures in clinical trials on chronic pain [44]. The HADS is a validated 14-item self-report screening scale (ranging from 0 to 3) including two subscales (i.e., anxiety and depression symptoms) [46, 47].

*Pain catastrophizing* will be measured using the Pain Catastrophizing Scale (PCS) [48]. This questionnaire includes three subscales (i.e., rumination, magnification, and helplessness). It consists of 13 items on a 5-point Likert scale ranging from 0 (not at all) to 4 (always) and has been validated [48].

*Psychological flexibility* will be measured with the Psychological Inflexibility in Pain Scale (PIPS) [49, 50]. This is a validated 12-item measurement, including two subscales (i.e., avoidance and cognitive fusion) [51]. It consists of a 7-point Likert scale, ranging from 0 (never true) to 6 (always true).

*Mindfulness* will be measured using the Freiburg Mindfulness Inventory (FMI) [52]. This validated measurement consists of 14 items with two subscales (i.e., presence and acceptance) [52]. It includes a 4-point Likert scale, ranging from 0 (rarely) to 3 (almost always).

*Values-based living* will be measured with the Engaged Living Scale (ELS) [53]. This is a validated 16-item measurement, consisting of two subscales (i.e., valued living and life fulfillment) [53]. It includes a 5-point Likert scale, ranging from 0 (completely disagree) to 4 (completely agree).

### Intervention evaluation

*Intervention evaluation* includes 15 questions regarding the evaluation of the intervention. It includes questions regarding amount of use and overall satisfaction with the content and guidance, which was based on an earlier RCT studying an online ACT intervention [33]. Overall satisfaction will be measured using the Client Satisfaction Questionnaire (CSQ-8) [54]. Also, participants will grade the intervention on a scale from 1 (extremely poor) to 10 (excellent).

#### Process outcomes

Technical data regarding usage of the intervention will be gathered, namely moment when session was first viewed, moment when session was finished, moment of message sent to supervisor, and moment of feedback given by supervisor. This enables evaluation of adherence to the intervention and information about the use of guidance. Once all participants have completed the online training, Karify will make this data available. Karify is the eHealth platform in which the online intervention was build (ISO 27001 and NEN 7510 certified).

#### Other outcomes

Qualitative data on intervention experiences and satisfaction will be collected by means of interviews with some participants after completion of the intervention. In this way, it will be possible to examine experiences, usage, usability, content fit of intervention with complaints, and satisfaction. Specifically, both participants who adhered and did not adhere to the intervention will be interviewed. Patients adhered to the intervention if all sessions were completed (i.e., based on data retrieved from Karify) and a minimum of 2 h per week was spent on the intervention (i.e., self-reported). Participants are informed about this by the information letter and informed consent form. As a starting point, 4 patients in each group (i.e., adherent and non-adherent) will be interviewed. New interviews will be done until saturation is reached.

#### Participant characteristics

Socio-demographic factors are assessed, including sex, marital status, having children, educational level, and work. Clinical information will be examined as well, including year of diagnosis, tumor type, other cancer treatments besides chemotherapy, CIPN characteristics (i.e., days per week, medication used to treat CIPN), long-term consequences of cancer (other than CIPN), and psychological problems. Comorbidities in the last 12 months will be examined using the Self-administered Comorbidity Questionnaire (SCQ) [55].

### Sample size calculation

Per group, 51 participants during follow-up measurements are necessary to detect minimal effect sizes of interest (*d* = .50) on the primary outcome. This is based on earlier findings on effectiveness of online and face-to-face ACT intervention for chronic pain [33, 34]. The power will be high enough (*p* = 1-beta = .80) to find significant effects in a two-sided test at alpha = .05. As found in previous online ACT interventions, a drop-out rate of 30% needs to be considered. G*Power calculations revealed that 73 participants per group are needed at baseline, which means that 146 participants are needed in total.

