### Statistical analysis

#### Primary analyses

Significant differences at baseline between the conditions will be checked by performing one-way ANOVA’s and chi-square tests.

Effects of the intervention on all outcomes will be assessed by performing intention-to-treat analyses using general linear mixed models. Baseline to post-intervention and 3- and 6-month follow-up differences will be used as repeated measures, with treatment (2 levels), time (3 levels) and their first-order interactions as fixed factors. Confidence intervals of 95% will be calculated for all outcomes. Drop-out and non-adherence are relatively common in online interventions [56]. Therefore, secondary analyses will be performed to examine effects on outcome variables for participants who adhered to the intervention (i.e., all session completed and self-reported minimum of 2 h per week spent on intervention). At post-intervention and follow-up, effect sizes (Cohen’s *d*) will be calculated using means and standard deviations. Effect sizes of 0.80 are considered large, effect sizes of 0.50 are evaluated as moderate, and effect sizes of 0.20 are considered small [57].

Initiative on Methods, Measurement, and Pain Assessment in Clinical Trials (IMMPACT) recommendations will be followed to evaluate the proportion of participants showing clinically significant change [58]. Clinical improvement will be assessed with missing values imputed by the Expectation Maximization-algorithm. Proportions of clinically improved participants and Chi-square tests will assess statistically significant differences in the proportions for the two conditions. It will be calculated for (a) pain interference (MPI – Interference), (b) pain intensity (NRS), and (c) CIPN symptom severity (EORTC QLQ – CIPN 20). A decrease of at least 0.6 standard deviation will be assessed as evidence of clinically significant change for the MPI – Interference scale, based on the IMMPACT guidelines [58]. Decreases of 20% or higher in pain intensity (NRS) will be assessed as minimum and moderate changes. No specific IMMPACT guidelines exist for the HADS. Therefore, a distribution-based decrease of at least 1 standard error of the mean is recommended [58].

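### The 51 per group behind the total of 146 does not follow from the stated two-sided test; it matches the one-sided sample size and gives about 71% power for d = 0.50, not 80%

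*Protocol article*

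**What the plan says.** The Sample size calculation section of the protocol article gives a complete calculation. The target is d = 0.50 on the primary outcome, pain interference, described as the smallest effect of interest. Power is set at 0.80 "to find significant effects in a two-sided test at alpha = .05". The number required at follow-up is given as follows: "Per group, 51 participants during follow-up measurements are necessary to detect minimal effect sizes of interest". The section then says that "a drop-out rate of 30% needs to be considered" and concludes that "73 participants per group are needed at baseline, which means that 146 participants are needed in total".

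The software named is G*Power. No test family, number of measurements, correlation or covariate is given.

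The Primary analyses section plans a mixed model on differences from baseline, "with treatment (2 levels), time (3 levels) and their first-order interactions as fixed factors". It names no baseline covariate.

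**The concern.** Sixty-four per group is the standard requirement for a two-sided, two-sample t-test with d = 0.50, 80% power and alpha 0.05. Fifty-one is the requirement for the one-sided version. The section states a two-sided test and reports the one-sided number, so its stated inputs and its result cannot both be right.

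This section is the only justification for the size of the trial. If the test is two-sided as stated, the calculation leaves about a 29% chance of missing the smallest effect of interest, where the reader is told 20%. Anyone relying on the stated 80% would give a non-significant result more weight as evidence against such an effect than the design supports.

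**Working it through.** **Inputs**, all from Sample size calculation: d = 0.50; alpha = 0.05, two-sided; power = 0.80; 51 per group at follow-up; 30% dropout; equal groups.

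**Method.** Power of the two-sample t-test with n per group, from the noncentral t distribution with df = 2n − 2 and noncentrality δ = d × √(n/2). This is the usual calculation for two independent means.

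**1. The plan's figure, two-sided as stated.**
- Solving for 80% power gives n = 63.8, so 64 per group.
- Normal approximation as a check: n = 2 × (1.960 + 0.842)² / 0.50² = 62.8, so 63.
- The stated 51 is not reproduced. The gap of 13 per group is too large to be rounding.

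**2. The same calculation, one-sided at alpha 0.05.**
- Solving for 80% power gives n = 50.15, so 51 per group, an exact match.
- One-sided power is 79.9% at 50 per group and 80.6% at 51.

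**3. Power at 51 per group.**
- df = 100 and δ = 0.50 × √25.5 = 2.525.
- Two-sided critical value 1.984: power = 70.6% (71.4% by normal approximation).
- One-sided critical value 1.660: power = 80.6%.
- Effect detectable with 80% power, two-sided: d = 0.56.

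**4. Dropout.**
- From 51: 51/0.70 = 72.9, so 73 per group and 146 in total. This reproduces the plan, so the inflation step is correct.
- From 64: 64/0.70 = 91.4, so 92 per group and 184 in total.

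**5. Could a more efficient analysis justify 51 in a two-sided test?** The correlation r between baseline and follow-up is not in the document, so a range is shown. Power is two-sided, for 51 per group at a single time point, with d on the raw-score SD.

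| r | Baseline-adjusted, effective d = 0.50/√(1 − r²) | Change score, effective d = 0.50/√(2(1 − r)) |
|---|---|---|
| 0.40 | 77.9% | 62.7% |
| 0.46 | 80.4% | 67.2% |
| 0.50 | 82.3% | 70.6% |
| 0.60 | 87.8% | 79.8% |

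Baseline adjustment reaches 80% from r of about 0.46. A simple change score needs r of about 0.60, and below r = 0.50 it does worse than the unadjusted comparison.

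A repeated-measures between-group test with f = 0.25 can also land near 51 per group: N = 104 in total (52 per group) with two measurements at r = 0.6, or with three at r = 0.7.

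**The case against.** The strongest reply is that 71% is the power of an analysis the trial will not run. It describes an unadjusted t-test at one time point on completers. The plan is an intention-to-treat mixed model over several follow-ups, which also uses the visits of people who drop out part-way. With baseline adjustment and r = 0.50, power would be 82%; if all 73 per group were retained, even the unadjusted two-sided test would have 85%. The one-sided origin is also only inferred: G*Power's repeated-measures routine gives about 52 per group under some settings, and those settings may stand in the full protocol that the article condenses. Finally, the plan promises 95% confidence intervals and effect sizes, which will show the precision achieved whatever power was planned.

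Parts of this stand. The one-sided origin is an inference from an exact match. The 71% belongs to the calculation as stated and is neither a floor nor a best estimate for the mixed model. Reporting confidence intervals reduces the risk that a null result is misread.

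It does not rescue the 51. Each alternative route needs a correlation or covariate that the section does not give. The Primary analyses section does not secure the gain either: it names no baseline covariate, and differences from baseline analysed as change scores could have less than 71% power. Baseline appears as a control variable only in the comparison of guided and unguided versions (Secondary analyses). Pooling over follow-ups is of limited help because the waiting-list group is offered the intervention at T4, so the 6-month contrast is no longer with an untreated control. Full retention contradicts the plan's own 30% dropout. Nor is this a detail left to another document, since the article prints a complete calculation whose result does not follow from its inputs.

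**Conclusion.** The concern holds. On the stated inputs the requirement is 64 per group at follow-up (92 per group and 184 in total at baseline), against the stated 51, 73 and 146. With 51 evaluable per group, an unadjusted two-sided comparison has 70.6% power for d = 0.50, and 80% power only for d = 0.56. The dropout arithmetic is right; the error is in the base figure.

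These figures assume equal groups, the plan's 30% loss in each arm and no baseline adjustment. The power of the planned mixed model could be higher or lower, depending on correlations that the document does not give. That the 51 came from a one-sided setting is very likely but not documented; the conclusion does not depend on it.

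**What to change.** Keep 146, since recruitment has been under way since December 2021, and correct the power statement in one of two ways.

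1. **Restate the power.** Suggested wording: *With 51 evaluable participants per group, an unadjusted two-sided comparison at alpha 0.05 has 71% power for d = 0.50, or 80% power for d = 0.56.* The cost is one sentence and a less favourable figure.

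2. **Base the power on a baseline-adjusted primary model.** State the assumed baseline-to-follow-up correlation and its source (at least 0.46 is needed for 80%), and write the baseline score into the primary analysis as a covariate. The cost is one covariate, already collected at T0.

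Either way, give the G*Power test family and settings so that the number can be reproduced. Neither option needs extra participants or a change to data collection.
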